### Data management {19}

All questionnaire data will be collected electronically and transferred to TSD (Services for Sensitive Data), alongside video and audiotape data. TSD is part of the research infrastructure at the Department of Psychology. File backups are automatically generated every 14 days. Only anonymized data will be shared with collaborators. We have permission to store de-identified data until 2037.

### Confidentiality {27}

All data are stored in TSD, which is an enclosed electronic storage system at the University of Oslo. All access to this database is strictly regulated. Only de-identified data will be shared between collaborators.

### Plans for collection, laboratory evaluation, and storage of biological specimens for genetic or molecular analysis in this trial/future use {33}

This is not applicable, as no biological data will be collected.

### Statistical methods

#### Statistical methods for primary and secondary outcomes {20a}

The main effect is measured as the difference between the intervention group and the waitlist group in SDQ scores from pre-intervention to 3 months, reported by siblings, parents, and teachers. This is investigated using mixed ANOVA, and effect sizes will be reported as Cohen’s *d*. To examine the effects beyond waitlist for the complete sample, we apply growth curve modeling, which enables us to investigate both mean changes at a group level over time and individual growth trajectories, with the inclusion of individuals with partial/missing data [26]. A series of linear mixed models are fitted. A model with only fixed and random intercepts serves as the null model, to which subsequent unconditional models of time will be compared. Finally, group membership and control variables are included in a set of conditional models, through which the longitudinal effect of the intervention is investigated. Growth curve models are fitted separately for the intent-to-treat sample and per-protocol, excluding participants with concomitant sibling care during follow-up. Multilevel analyses controlling for nesting (group and site level) are conducted with MPlus. Other analyses are conducted using updated versions of IBM SPSS and R.

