### Outcomes {12}

The primary outcome is sibling mental health, measured with the Strengths and Difficulties Questionnaire (SDQ) [14]. The 25-item SDQ is rated by siblings (self-report), as well as the participating sibling’s parents and main teacher, as proxy reports on sibling well-being. The SDQ covers five domains (emotional, conduct, inattention, peer problems, and prosocial behavior). We chose the SDQ as the primary outcome for the three main reasons. First, the SDQ has well-documented psychometric properties with this age group and substantial overlap with lengthier mental health measures (e.g., [15]). In our open trial, the SDQ showed good inter-item reliabilities (*α* = .77 to .82) and significant reduction from pre-intervention to 6-month follow-up, demonstrating good responsiveness to change. Second, the SDQ provides a continuous score and a clinical cutoff score. This enables us to report both mean change scores from pre-intervention to post-intervention, 3-, 6-, and 12-month follow-up, and the number of participants in the clinical, borderline, and normal range at each measurement point. Third, the SDQ includes strengths, an essential component for measuring well-being. Outcomes will be reported for sibling, parent, and teacher ratings.

Secondary outcomes cover additional risk factors for siblings linked to the World Health Organization’s well-being definition [16]: (1) family communication, because poor family communication is a documented risk factor in families of children with chronic illness [2]. It is measured with the Parent-Child Communication Scale (PCCS) [17], rated by siblings about parents and parents about siblings; (2) quality of life, because it represents a function-based indicator of well-being beyond mental health symptoms. It is measured with the KINDL Fragebogen [18] rated by siblings and parents (about siblings); (3) sibling adaptation, because it is a well-being variable tailored for siblings of children with chronic illness. It is measured with the Negative Adjustment Scale (NAS) [19], rated by siblings; and (4) sibling ND knowledge, because it is associated with sibling well-being [4]. It is measured with the Sibling Knowledge Interview (SKI) [6], conducted with siblings over the phone by trained clinicians. All secondary outcomes have demonstrated internal consistency (*α* = .90 for KINDL [18]; *α* = .75 to .82 for PCCS [11, 17]; *α* = .79 for NAS [6]; *α* = .78 for SKI [11]).

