### Sample size {14}

The planned sample is 288 siblings, 288 mothers, and 288 fathers. Based on a power analysis of change in the main outcome variable (SDQ) from our open trial, with a minimal relevant standardized effect size of 0.4, a statistical power of .8, and a significance level of .05 [24], we need a sample of 136 families. The intra-cluster correlation coefficient (ICC) in our open trial was 0.11. We have taken this lack of independence between observations into account in sample size estimates. The planned group size is 6, which results in an inflation factor (IF) of 1.55 (IF = 1 + (*m* − 1) × ICC) [25]. Adjusting with this IF resulted in a sample size of 211 (IF × 136). We further increased the sample to 288 to compensate for dropouts and concomitant care (estimated to 27% based on our open trial). An estimated 5000 children with ND aged 0–18 years receive health services in the catchment area, of whom an estimated 1000 (20%) have at least one sibling aged 8–16 years. Thus, a 29% response rate is required to reach our sample size. We believe this is a realistic goal given the response rate in our open trial was 58%, and whereas one site recruited 107 participants in our open trial, we now have eight sites.

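### The main effect is defined on sibling, parent and teacher SDQ ratings with none named as primary and no success rule, although the trial is sized for one SDQ variable at a single .05 level

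*Protocol article*

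**What the plan says.** The section Statistical methods for primary and secondary outcomes {20a} defines the main effect as the between-arm difference "in SDQ scores from pre-intervention to 3 months, reported by siblings, parents, and teachers", to be examined by mixed ANOVA. The section Outcomes {12} makes sibling mental health, measured with the SDQ, the primary outcome. It lists the sibling, the parents and the main teacher as raters, describes the parent and teacher ratings as proxies, and closes with "Outcomes will be reported for sibling, parent, and teacher ratings".

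The section Sample size {14} refers to the SDQ as a single main outcome variable. It plans "with a minimal relevant standardized effect size of 0.4", with "a statistical power of .8, and a significance level of .05", and concludes "we need a sample of 136 families" before inflation. It does not say whose SDQ rating this is. The same section states "The planned sample is 288 siblings, 288 mothers, and 288 fathers", and Eligibility criteria {10} says that both parents supply data whichever of them attends. Nothing says whether the two parent ratings are averaged, analysed separately or reduced to one.

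**The concern.** Research question 1 in Objectives {7} is a yes-or-no question: does the intervention improve sibling mental health compared with waitlist? To answer it, the plan needs either one primary variable or a rule that turns several ratings into one conclusion. The text provides neither, while giving three ratings equal standing in the definition of the main effect. The sample size therefore belongs to no identified score.

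Raters may plausibly disagree. Siblings and participating parents cannot be masked and rate their own family's experience, whereas teachers do not attend the sessions. If one rating shows an effect and the others do not, the conclusion would have to be chosen after the data are seen. The article presents the trial as the step that would establish an evidence base for the intervention, so the ambiguity sits on the claim that matters most.

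**Working it through.** **1. The plan's own figures (Sample size {14}).** Inputs: effect size 0.4, power .8, significance level .05, 136 families, ICC 0.11, groups of 6, loss of 27%.

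- Inflation factor: 1 + (6 − 1) × 0.11 = 1.55. Then 1.55 × 136 = 210.8, so 211, as stated.
- Allowance for loss: 211 / (1 − 0.27) = 289, against the stated 288 = 6 × 48. This agrees closely.
- The 136 does not follow from the printed inputs alone. A two-sided two-sample comparison needs about 198 in total. An unstated pre-post correlation of about 0.55 (ANCOVA) or 0.65 (change score) would give 136. Since the text refers to a power analysis of change, this may be the explanation, and the present point does not depend on it. What matters here is that the calculation covers one SDQ comparison at one .05 level.

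**2. Number of ratings.** Three rater types are named in {12} and {20a}. If mother and father are analysed separately, there are four ratings.

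**3. Familywise error if any one significant rating counts as success.** Each rating is taken to be tested two-sided at .05. For k independent tests the rate is 1 − 0.95^k:

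- k = 3: 1 − 0.95³ = 0.143
- k = 4: 1 − 0.95⁴ = 0.185

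Ratings of the same child are likely to be positively correlated, which lowers these rates. The document gives no correlation between raters, so the values below are assumptions. The test statistics are treated as equally correlated normal variables. The last two columns count only false claims of benefit, for which the nominal rate is 2.5%.

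| Assumed correlation | 3 ratings, either direction | 4 ratings, either direction | 3 ratings, benefit only | 4 ratings, benefit only |
|---|---|---|---|---|
| 0 | 14.3% | 18.5% | 7.3% | 9.6% |
| 0.3 | 13.6% | 17.4% | 6.8% | 8.7% |
| 0.5 | 12.5% | 15.6% | 6.3% | 7.8% |
| 0.6 | 11.8% | 14.4% | 5.9% | 7.2% |
| 0.8 | 9.8% | 11.4% | 4.9% | 5.7% |

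With four ratings, a mother-father correlation of 0.6 and 0.2 to 0.3 for the other pairs, the rate is 16.9%.

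**4. Other ways out.**

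- One named primary rating at .05: the error is 5% and no extra participants are needed.
- All ratings must be significant: no inflation, but power falls below that of a single test.
- Bonferroni over three ratings at .0167 each, keeping 80% power on each: the sample size factor is ((2.394 + 0.842) / (1.960 + 0.842))² = 1.33. Then 136 becomes about 182, and 182 × 1.55 / 0.73 is about 386, against 288 planned.

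**The case against.** The strongest reply is that the error rate follows from a decision rule that the article never states. The .05 appears only in the power analysis. Section {20a} sets no level per rater and does not say that one significant rater is enough. If all raters had to succeed, there would be no inflation. This stands, and the rates above are therefore conditional. A reader might infer that the trial has a fixed false-positive risk approaching 19%. The text does not support that: 18.5% needs an any-one-suffices rule, mother and father analysed separately, and four independent ratings, although two of the raters would be parents of the same child. For the three named types the ceiling under independence or positive correlation is 14.3%.

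Second, the adjustment method may sit in an analysis plan or in the full protocol, neither of which is shown, and the schedule table is not legible here. It would therefore be wrong to conclude that no error control exists. Which variable is primary is a different matter. It belongs in the outcome section, and the published text gives three ratings equal standing rather than leaving the choice open.

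Third, using several informants is deliberate: Table 1 presents it as an answer to earlier trials that relied on single raters. The article also commits to reporting all three ratings and to publishing null findings. That limits concealment, and nothing suggests that selective reporting is intended. It does not say what is concluded when the ratings differ.

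Finally, a reader might add an inflation from clustering to these rates. Section {20a} provides for multilevel analyses by group and site. Whether these cover the main contrast is a separate question, and the figures here do not involve it.

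**Conclusion.** The point holds as a defect in the definition of the primary endpoint. The main effect spans three ratings of equal standing, the sample size is for one, and no visible text ranks or combines them or sets a success rule. Research question 1 is undetermined whenever raters disagree.

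If any one rating at two-sided .05 suffices, the familywise error is about 12-14% for the three rater types and about 16-18% with separate parent ratings, for assumed correlations up to about 0.5. Stronger correlation lowers it: with three ratings at 0.8 it is still about twice the nominal 5%. For false claims of benefit alone the rates are roughly half, against 2.5%. Because the primary claim is affected, the matter should be settled before outcomes are compared by arm.

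**What to change.** In sections {12}, {14} and {20a}, before any comparison by arm, define one primary variable by three elements:

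- **Informant.** Sibling self-report is the natural default, since the article treats the other ratings as proxies. If parent report is preferred, fix which parent.
- **Score.** State which SDQ score is meant; {12} lists five domains, including prosocial behaviour.
- **Assessment.** Tie it to the single post-intervention/post-waitlist assessment at about 12 weeks that forms the main contrast. The text now describes this time point in different ways: 12 weeks post in the abstract, 3 months in {20a}, and an immediate post-intervention point in the legend to Fig. 2. Questionnaires are completed online, so it should be defined as an assessment window and not as a visit.

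Keep the other raters' SDQ scores as reported secondary outcomes, tested in a fixed order or with Holm adjustment if confirmatory claims are wanted on them. Tie the power statement to the named score.

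The cost is a change of wording in three sections and no additional participants. The downside is that success can no longer be claimed on another rater alone.

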### Assignment of interventions: allocation

#### Sequence generation {16a}

Participants are randomly assigned to either intervention or 12-week waitlist (1:1), in clusters of 6, stratified by participant age to avoid > 4-year age gaps between participants in the intervention groups. Each site requests a randomization number when the site has ~ 6 consenting participants within each age range. A pre-generated randomization indicates whether the cluster will be either intervention or waitlist. The allocation sequence was computer-generated by a research coordinator who is independent of the PI. The sites and participants are advised of their allocation approximately 2 weeks prior to group dates, to respect their time management needs (e.g., planning time off school and work for participants; allowing time for other clients for group leaders). Participants allocated to waitlist receive the intervention after 12 weeks. The dates for the potential waitlist groups are included in the original invitation letter to ease families’ planning.

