Across sites, the general procedure principle is that each site coordinator contacts the central project coordinator when they have at least 5 consenting participants. For each intervention group, 3–8 consenting families are required to allocate a randomization number. Participants receive all pre-intervention questionnaires approximately 1 month before the set group date, with regular reminders if not completed. Approximately 2 weeks before the set group date, families and group leaders are informed by the central research coordinator about whether the group was allocated to intervention or waitlist. If assigned to waitlist, participants receive the baseline questionnaires again 2 weeks before the intervention date (approximately 12 weeks after the initial group date). The aim is to conduct 48 groups over the project period. We have pre-generated a randomization list with 100 numbers, ensuring that there will never be more than 3 allocations to the same arm in a row (i.e., intervention or waitlist). This way, the number of participants in both arms will be somewhat balanced if we have to end the trial before reaching our aim of 48 groups, or if we need to increase the number of groups due to < 6 families per group (the aim is 288 families, i.e., 6 × 48).

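### Whole groups are randomised, but the main SDQ comparison is assigned to a mixed ANOVA and the promised multilevel adjustment is not tied to it

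*Protocol article*

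**What the plan says.** The unit of allocation is the group. Sequence generation {16a} of the protocol article states: "A pre-generated randomization indicates whether the cluster will be either intervention or waitlist". Implementation {16c} gives one randomisation number per group ("For each intervention group, 3–8 consenting families are required to allocate a randomization number") and sets the scale: "The aim is to conduct 48 groups over the project period".

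Sample size {14} recognises the consequence. It reports "The intra-cluster correlation coefficient (ICC) in our open trial was 0.11", continues "The planned group size is 6, which results in an inflation factor (IF) of 1.55", and says: "We have taken this lack of independence between observations into account in sample size estimates".

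Statistical methods {20a} first defines the main effect as the difference between arms in SDQ from pre-intervention to 3 months, and then says: "This is investigated using mixed ANOVA". It next introduces growth curve (linear mixed) models for effects beyond the waitlist period. Towards the end of the section comes: "Multilevel analyses controlling for nesting (group and site level) are conducted with MPlus". Other analyses are assigned to SPSS and R. The section does not say whether the main comparison belongs to the multilevel analyses or to the others.

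**The concern.** A mixed ANOVA with arm as the between-subject factor and time as the within-subject factor takes its error term from differences between individual siblings. It has no component for the group in which they were randomised. With two time points, the arm-by-time test is a two-sample comparison of individual change scores. If changes are correlated within randomised groups, that comparison understates the standard error of the difference between arms.

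This is the confirmatory contrast of a trial meant to establish an evidence base for the intervention. An understated standard error gives confidence intervals that are too narrow and a false-positive rate above the stated .05. The plan would also be inconsistent with itself: it recruits extra families to pay for clustering and then names a primary test that does not use that allowance. Where the ANOVA and a nesting-adjusted model lead to different conclusions, the article does not say which one decides.

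**Working it through.** **Inputs from the protocol article.** Planned group size m = 6, ICC = 0.11, α = .05, unadjusted sample 136, and 27% allowed for dropout and concomitant care (all Sample size {14}). Group size range 3–8 and 48 groups (Implementation {16c}). 1:1 allocation (Sequence generation {16a}), so about 24 groups per arm. Sidedness is not stated; two-sided is assumed.

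**Reproducing the plan's own figures.**
- Inflation factor: IF = 1 + (m − 1) × ICC = 1 + 5 × 0.11 = 1.55, as stated.
- 136 × 1.55 = 210.8, rounded to 211, as stated.
- 211 / 0.73 = 289, against 288 stated (48 × 6). This agrees within rounding.

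Clustering therefore adds 211 − 136 = 75 families before the allowance for loss.

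**Effect of leaving the group out of the test.** The variance of the difference between arms is larger by IF than the test assumes, so its standard error is too small by √1.55 = 1.245. The true two-sided type I error is

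2 × [1 − Φ(1.96 / √IF)].

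At m = 6 this is 2 × [1 − Φ(1.96 / 1.245)] = 2 × [1 − Φ(1.574)] = 11.5%.

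**Sensitivity to the assumptions.** If only intervention groups cluster, the variance factor is the average of the two arms, (IF + 1)/2.

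| Scenario | Variance factor | True type I error |
|---|---|---|
| ICC 0.11 in both arms, m = 3 | 1 + 2 × 0.11 = 1.22 | 7.6% |
| ICC 0.11 in both arms, m = 4.38 | 1 + 3.38 × 0.11 = 1.372 | 9.4% |
| ICC 0.11 in both arms, m = 6 | 1.55 | 11.5% |
| ICC 0.11 in both arms, m = 8 | 1 + 7 × 0.11 = 1.77 | 14.1% |
| ICC 0.11 in intervention arm only, m = 4.38 | (1.372 + 1)/2 = 1.186 | 7.2% |
| ICC 0.11 in intervention arm only, m = 6 | (1.55 + 1)/2 = 1.275 | 8.3% |
| ICC 0.05 in both arms, m = 4.38 to 6 | 1.169 to 1.25 | 7.0–8.0% |
| ICC 0.01 in both arms, m = 4.38 to 6 | 1.034 to 1.05 | 5.4–5.6% |

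Here m = 4.38 is 6 × 0.73, the group size left if the whole 27% is removed. That is a lower limit for the intent-to-treat analysis. The 27% includes concomitant care, and Statistical methods {20a} excludes siblings with such care only from the per-protocol analysis.

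**Check by simulation** (24 groups per arm, 20,000 runs, no true effect):

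| Scenario | Test ignoring groups | Test on group means |
|---|---|---|
| ICC 0.11 in both arms, m = 6 | 11.4% | 4.7% |
| The same, with 27% of siblings lost at random | 10.0% | 5.2% |
| ICC 0.11 in intervention arm only, m = 6 | 8.2% | 5.0% |
| ICC 0, m = 6 | 4.7% | 4.8% |

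The simulation agrees with the formula. An analysis at the level of the randomised group holds about 5% in every scenario run.

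**The case against.** The strongest reply is that the same section does promise an adjustment for group and site. It is headed as covering both primary and secondary outcomes, and the sentence on multilevel analyses is not restricted to the growth curves. The authors plainly knew of the clustering, since they sized the trial for it. A reader might infer from the naming of a mixed ANOVA that the primary test certainly treats siblings as independent. The article does not say that: the multilevel sentence is neither tied to the main comparison nor excluded from it. This part of the reply stands, and it makes the finding conditional. It does not remove the finding, because the only method named for the main effect is one that ordinarily omits the group.

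The second reply concerns size. The ICC comes from an open trial in which every group received the intervention, and the article does not say whether it refers to SDQ level or SDQ change. The arm-by-time test concerns change, from which stable differences between groups cancel. Waitlist groups have also not yet had their sessions when the main contrast is measured, so they may cluster less. This stands as well: 11.5% is one scenario, and the lower rows of the table are plausible.

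A third reply is that a condensed article leaves model detail to the full protocol or analysis plan. That holds for covariates and the degrees-of-freedom method. It does not hold for the primary test itself, which the article names.

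A reader might also want to add family as a missing level, since Eligibility criteria {10} lets more than one sibling per family attend. The target is 288 siblings and equally 288 families, the article gives no number of sibling pairs, and a group effect already covers pairs who share a group. The article does not support more than a side remark on this.

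**Conclusion.** The point holds in conditional form. The article randomises groups, sizes the trial for their correlation, and then fixes a mixed ANOVA for the main SDQ comparison without connecting the promised multilevel adjustment to it. If that ANOVA is run in its ordinary form, the nominal 5% test has a true two-sided type I error of about 11.5%. This assumes six per group and an ICC of 0.11 that applies to SDQ change in both arms. The rate is about 8–14% over the allowed group sizes, about 7–8% at 4.38 to 6 per group if only intervention groups cluster or the ICC of change is 0.05, and close to 5% if that ICC is about 0.01.

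A reader might take a rate near 10% as an established property of this trial. The documents do not support that, because they fix neither the ICC of change, nor the clustering in waitlist groups, nor the omission of the group term. The need to name a primary analysis that respects the unit of randomisation depends on none of these unknowns.

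**What to change.** In Statistical methods {20a}, state that the primary 12-week SDQ comparison is a multilevel (linear mixed) model with a random effect for the randomised group, or an equivalent cluster-level analysis. Inference should be based on the roughly 48 groups and not on the number of siblings. Keep the mixed ANOVA as descriptive only. Covariates, the treatment of site and the small-sample method can be left to the analysis plan.

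The cost is a change of wording. The multilevel software is already planned, and neither recruitment nor data collection changes. At six per group with ICC 0.11 in both arms, confidence intervals would be about 1.245 times as wide as those from the unadjusted test. The sample size was inflated for exactly this. With a smaller ICC the widening is less.

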### Objectives {7}

Objective 1 is to promote sibling well-being by addressing research question 1: *Does the SIBS intervention improve mental health for siblings of children with ND compared to waitlist?* and research question 2: *What are the long-term trajectories of sibling well-being, in terms of mental health, family communication, quality of life, sibling adaptation, and disorder knowledge from pre-intervention to 12-month follow-up?* Based on the findings from our open trial, we hypothesize that the SIBS intervention will outperform waitlist and that the mean 12-month trajectories will indicate significantly improved well-being. Objective 2 is to identify those siblings who are most likely to benefit from the SIBS intervention by addressing research question 3: *Which factors (i.e., ND impairment, parent mental health, family stress) predict outcomes of the SIBS intervention?* Previous findings indicate higher ND impairment and poorer parent mental health will be associated with poorer sibling mental health [1, 3]. However, there is limited knowledge upon which to base hypotheses about predictors of effects. The third research question is therefore exploratory. SIBS-RCT represents a major contribution to the research and practice field towards establishing an evidence-based intervention for siblings. In the event that intervention and waitlist are no different, the impact of SIBS-RCT is still substantial in that we will aim to identify (a) participant subgroups that show positive response and (b) effective components of the SIBS manual, by examining group leader adherence as an outcome predictor. This will allow us to continue to re-engineer SIBS-RCT iteratively to improve outcomes, and avoid promotion of a less-than-optimal intervention.

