### Data collection and management

#### Plans for assessment and collection of outcomes {18a}

Primary and secondary outcomes are collected at pre- and post-intervention, plus 3-, 6-, and 12-month follow-up. Participants randomized to waitlist repeat outcome measures after waitlist (see Table 2 for details). While a 12-week waitlist weakens our ability to prove long-term effectiveness of the SIBS intervention, we find it unethical to make vulnerable siblings wait > 12 weeks for an intervention we expect will reduce their symptoms. All questionnaires are collected electronically using “Nettskjema,” an online questionnaire system run by the University of Oslo IT Department. Participants receive a link to the questionnaires via email. The system has built-in features to detect and prevent data entry errors and missing data. To help reduce/prevent dropout, several reminders are sent to participants at every measurement point. If a participant misses a measurement point, they still receive an invitation and reminders at the next measurement point (unless they actively withdraw from the study). Children can respond via their own or their parents’ email address.

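### Beyond week 12 the growth-curve models look for the intervention's longitudinal effect through trial arm, but by then both arms have been treated

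*Protocol article*

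**What the plan says.** All references are to the Protocol article.

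- **Model and purpose.** Section {20a} sets the growth curves apart from the main 12-week comparison: "To examine the effects beyond waitlist for the complete sample, we apply growth curve modeling". After null and time-only models, it says that "group membership and control variables are included in a set of conditional models, through which the longitudinal effect of the intervention is investigated".
- **Crossover.** Sequence generation {16a}: "Participants allocated to waitlist receive the intervention after 12 weeks".
- **Measurements.** Section {18a}: "Primary and secondary outcomes are collected at pre- and post-intervention, plus 3-, 6-, and 12-month follow-up", and "Participants randomized to waitlist repeat outcome measures after waitlist". The key to Table 2 counts the 3-, 6- and 12-month visits from the intervention. Implementation {16c} places the repeat waitlist questionnaire about 2 weeks before that arm's own group date.
- **Hypothesis.** Objectives {7} expects that "the mean 12-month trajectories will indicate significantly improved well-being".
- **Caveat.** Section {18a} concedes that "a 12-week waitlist weakens our ability to prove long-term effectiveness".

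The article gives no treatment status that changes at crossover, no break in the time axis at that point and no time origin for these models.

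**The concern.** A term for randomised arm estimates a treatment effect only while one arm is untreated. Here that holds for about 12 weeks. Later, arm separates families treated early from families treated about three months later. Section {20a} nevertheless gives this term the job of showing the longitudinal effect, in an analysis whose stated purpose is the period beyond waitlist. Term and target do not match.

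Two misreadings are then possible. A real and lasting benefit could appear as little or no longitudinal effect, or as slightly better change on waitlist. Conversely, the pooled improvement over 12 months has no untreated comparator after week 12, so natural improvement or regression to the mean could pass for a benefit. The stakes are in the long-term results. The abstract says all outcomes will also be examined by growth curves, and section {20c} names the same models as the way to handle participant-level missing data.

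**Working it through.** The article states no figure for these models, so there is none to reproduce. The check asks what the arm-by-time term would show if the intervention works.

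**Inputs from the article.** Effect 0.4 SD, the minimal relevant effect in Sample size {14}, coded -0.4 because a lower difficulties score is better; waitlist treated at about 12 weeks; follow-up counted from own intervention.

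**Assumptions.** The model has group and group-by-time terms, the usual form of a conditional growth model. There is no change other than the treatment effect. Visit times are as listed below.

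**Hand check: effect immediate and permanent.** Slope = Σ(t - t̄)y / Σ(t - t̄)².

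*Months from the first group date*
- Intervention arm: t = -1, 0.25, 3.25, 6.25, 12.25 (mean 4.2); y = 0, then -0.4 four times. The last four deviations sum to 5.2, so the slope is -0.4 × 5.2 / 112.55 = -0.0185 SD per month.
- Waitlist arm: t = -1, 2.3, 3, 6, 9, 15 (mean 5.717); y = 0, 0, then -0.4 four times. The last four deviations sum to 10.133, so the slope is -0.4 × 10.133 / 161.21 = -0.0251 SD per month.
- Difference, intervention minus waitlist: about +0.007 SD per month, which favours waitlist.

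*Five equally spaced waves, with the waitlist arm's post measure taken after waitlist*
- Σ(t - t̄)² = 10.
- Intervention: -0.4 × 2 / 10 = -0.08 per wave. Waitlist: -0.4 × 3 / 10 = -0.12 per wave.
- Difference: +0.04 per wave, or +0.16 over four steps.

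*Clock from own intervention, with the post-waitlist measure as the waitlist baseline*
- Both arms have the same times and the same means, so group and group-by-time are both exactly 0.

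**Other effect shapes.** These are expected fixed effects from a random-intercept model with linear time and within-person correlation 0.6 (assumed). Assumed visit weeks are 0, 1, 13, 26, 52 (intervention) and 0, 12, 14, 26, 39, 65 (waitlist).

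| True effect, -0.4 SD at its largest | Own clock | Baseline clock, per 52 weeks | Wave clock, over 4 steps |
|---|---|---|---|
| Immediate, lasting | 0.00 | +0.10 | +0.16 |
| Builds over 12 weeks, lasting | 0.00 | +0.01 | +0.01 |
| Builds over 26 weeks, lasting | 0.00 | -0.03 | +0.01 |
| Builds linearly over 52 weeks | 0.00 | -0.05 | 0.00 |
| Peaks at 12 weeks, then fades | 0.00 | +0.08 | +0.01 |
| Immediate, then fades | 0.00 | +0.15 | +0.16 |

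A random slope leaves the linear results unchanged. A quadratic in time since baseline does not repair them. For the immediate lasting effect, the modelled change in arm gap is +0.06 at week 13 and +0.27 at week 52, where the truth is -0.40 and 0.

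**Check of the alternative.** Replace arm by an indicator that is 0 before and 1 after own intervention, with a common linear time trend. The immediate lasting effect is recovered as -0.400, and still as -0.400 when a secular trend of -0.2 SD per year is added. For the effect that builds over 12 weeks, the indicator alone gives -0.162, so a term for time since own intervention is needed as well.

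**The case against.** **The faulty model is partly inferred.** Section {20a} spells out no interaction, time origin or shape of time, and such detail may sit in the full protocol or analysis plan. That stands, and it makes every coefficient above illustrative. It does not remove the mismatch, because the article itself names the sample, the term and the effect the term is meant to show. The same section also uses group for the nesting level. Arm is the likelier meaning, and a delivery-group term would not identify an intervention effect either.

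**Some of the shortfall comes from fitting a line to a step.** On the hand-check figures, -0.0185 × 13.25 months is about -0.25, so even a never-treated control arm would not return -0.4 under linear time. With categorical time and wave coding, the arm contrast at the post measure is exactly -0.4. Both points stand. But that contrast is the comparison before crossover; it says nothing about effects beyond waitlist.

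**Research question 2 is about mean change.** It asks for trajectories from pre-intervention to 12 months, which the time terms describe. On the own-intervention clock a null arm term is what one should expect, since both arms then follow the same treated course. This stands. A reader might infer that research question 2 cannot be answered, and the article does not support that. What is lost is a controlled reading of the answer.

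**The limitation is disclosed.** Section {18a} does so, but the model is not adapted to it.

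**Conclusion.** The point holds as a mismatch between a stated model term and its stated purpose. After about week 12, arm contrasts early with delayed treatment and cannot estimate the intervention's longitudinal effect.

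For a lasting 0.4 SD benefit the arm-by-time term is zero on the own-intervention clock. On a baseline clock it ranges from +0.10 to -0.05 SD per 52 weeks, and on a wave clock from +0.16 to about zero over four steps, depending on how fast the benefit appears. These sizes rest on the inferred group-by-time term, assumed visit times and, for the table, an assumed correlation of 0.6.

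Three stronger readings are not supported:

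- That the term is always zero or reversed. Slowly building effects keep the right sign on a baseline clock, though strongly attenuated.
- That the main result is compromised. The mixed ANOVA from pre-intervention to 3 months compares the arms before the waitlist arm is treated.
- That the secondary outcomes rest on the growth curves alone. The mixed ANOVA is described only for the primary measure, but the abstract presents growth curves as an additional analysis of all outcomes.

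**What to change.** 1. In the longitudinal models, stop using arm as the carrier of the effect. Use a time-varying treatment status (0 before, 1 after own intervention) plus time since own intervention, with a common time-since-baseline term. Let time since own intervention bend, for example with a break at the 3-month visit, so that an effect that builds and then levels off can be followed.
2. Keep the post-waitlist measure as an untreated observation. Together with the waitlist baseline it is what identifies natural change.
3. Take randomised arm contrasts, including those for secondary outcomes, only from data up to the 12-week visit.
4. Describe later trajectories as uncontrolled within-person change, and reword section {20a} and the hypothesis in Objectives {7} so that neither presents them as the intervention's longitudinal effect.

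**Cost.** Revised wording and a recoded variable; no new data or visits. The claim about 12-month results becomes weaker. The model also relies on a time trend common to both arms that continues in the assumed form after crossover, which no untreated observation can check.
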